## Abstract

**Background:**

Seasonal allergic rhinitis (hayfever) is common and can contribute to a considerable reduction in the quality of life of adolescents. This study aims to examine the effectiveness of standardised allergy training for healthcare professionals in improving disease-specific quality of life in adolescents with hayfever.

**Methods/Design:**

Adolescents with a history of hayfever registered in general practices in Scotland and England were invited to participate in a cluster randomised controlled trial. The unit of randomisation is general practices.

The educational intervention for healthcare professionals consists of a short standardised educational course, which focuses on the management of allergic rhinitis. Patients in the intervention arm of this cluster randomised controlled trial will have a clinic appointment with their healthcare professional who has attended the training course. Patients in the control arm will have a clinic appointment with their healthcare professional and will receive usual care.

The primary outcome measure is the change in the Rhinoconjunctivitis Quality of Life Questionnaire with Standardised Activities (RQLQ(S)) score between baseline and six weeks post-intervention in the patient intervention and control groups.

Secondary outcome measures relate to healthcare professionals' understanding and confidence in managing allergic rhinitis, changes in clinical practice, numbers of consultations for hayfever and adolescent exam performance.

A minimum of 11 practices in each arm of the trial (10 patients per cluster) will provide at least 80% power to demonstrate a minimal clinically important difference of 0.5 in RQLQ(S) score at a significance level of 5% based on an Intraclass Correlation Coefficient (ICC) of 0.02.

**Discussion:**

At the time of submission, 24 general practices have been recruited (12 in each arm of the trial) and the interventions have been delivered. Follow-up data collection is complete. 230 children consented to take part in the trial; however complete primary outcome data are only available for 160. Further recruitment of general practices and patients will therefore take place in the summer of 2010.

**Trial Registration:**

Current Controlled Trials ISRCTN95538067

## Background

In the UK, allergic diseases have an overall lifetime prevalence of about 30% in the general population, with a considerably higher prevalence in young people [1,2]. Intermittent allergic rhinitis (also known as seasonal allergic rhinitis or hayfever) affects up to 30% of adults and 40% of children at some time in their lives [2-5] Up to 80% of patients with asthma also have allergic rhinitis, and nearly 40% of those with allergic rhinitis have co-existing asthma [6,7]. Allergic rhinitis and its major co-morbidity asthma cause significant health burdens to the individual, and the impairment of quality of life experienced by patients with rhinitis is at least as severe as that of patients with asthma [8]. A recent editorial in *TheLancet *reported that the economic burden posed by allergic rhinitis has almost doubled since 2000 [9].

The Allergic Rhinitis in Asthma (ARIA) classification scheme was introduced in 2001 and reinforced in 2008; this subdivides allergic rhinitis into "intermittent" or "persistent" disease [8,10]. Previously, allergic rhinitis was subdivided based on time of exposure into "seasonal" (more commonly known as hayfever), "perennial" and "occupational" forms. Intermittent allergic rhinitis (IAR) is defined as symptoms being present for less than four days per week for less than four weeks and persistent allergic rhinitis refers to symptoms that are present for more than four days a week and for more than four weeks. This new ARIA classification has not yet been widely adopted in UK primary care, and patients with IAR are thus still given a Read code [11] for seasonal allergic rhinitis in their medical records and hence these terms and codes need to be searched when identifying local populations.

Common symptoms of allergic rhinitis include sneezing, itching, watery rhinorrhoea and nasal blockage, and these can have a considerable negative impact on children in terms of their physical, social and psychological well-being, and academic performance. Research has, for example, shown that children with allergic rhinitis indicated that they experienced particular problems with their schoolwork [12], and a recent case control study of teenage hayfever sufferers showed an association with an increased risk of unexpectedly dropping a grade in summer examinations (adjusted odds ratio 1.43; 95% CI 1.13-1.81) [13]. Children may also lose sleep, have reduced ability to concentrate, and have a risk of developing a major depressive disorder [14]. The achievement of optimal outcomes in children with allergic rhinitis depends on timely diagnosis, followed by implementation of measures to reduce allergen exposure, selection of safe and effective treatments and patient adherence to therapeutic regimens. This can be facilitated by appropriate training of healthcare professionals (HCPs) and patients in the optimum treatment choices, timing of medication commencement, appropriate techniques to ensure appropriate delivery of intranasal treatments and ensuring that compliance remains optimal.

Treatments for allergic rhinitis aim to minimise or eliminate symptoms, optimise quality of life and reduce the risk of developing co-morbidities. A report published in 2003 *Allergy - the unmet need*, commissioned by the Royal College of Physicians, clearly demonstrated current deficiencies in allergy services in the UK, and made a number of proposals to improve patient care, both in primary-and secondary-care. These findings have been confirmed in relation to allergic rhinitis in a UK survey of general practitioners whose practice had a self-declared interest in the management of allergic and respiratory disorders [15], which found considerable variation in their awareness and management of allergic rhinitis. This again suggests that an educational intervention covering all aspects of management of allergic rhinitis in primary care is both timely and important.

The House of Lords Science and Technology Committee report on Allergy (2006-7) recommended that the Department for Children, Families and Schools should review the clinical care that children receive at school, and should reassess the way they are supported through the examination season [16]. However, the knowledge and training in allergic diseases of teachers and support staff may not be sufficient to support children though this period. Enhancing the role of primary care professionals in ensuring control of allergy symptoms by improving training and engaging the patient in self-care may be a more beneficial and safer approach.

A multi-centre community based randomised controlled trial showed that standardised allergy education given to HCPs improved disease-specific quality of life in patients with perennial rhinitis [17]. This study found that a structured educational intervention was feasible to deliver in primary care, was well received by GPs and nurses, and improved outcomes in adults with perennial rhinitis. The present trial is building on this by testing the effectiveness of a modified version of this educational intervention in adolescents with hayfever.

### Aims of the study

The primary aim of this study is to examine the effectiveness of standardised allergy training in increasing disease-specific quality of life of adolescents with hayfever. A customised one-day short course, which focuses on allergic rhinitis and its main co-morbidity asthma, will be delivered to health care professionals.

The secondary aims are to examine whether attending an allergic rhinitis and asthma short course can enhance knowledge and skills of practitioners who consult with hayfever sufferers, changes in clinical practice, numbers of consultation for hayfever and adolescent exam performance.

### Specific objectives

1. To evaluate the effectiveness of standardised allergy training for HCPs on adolescent (12-18 years) rhinitis-specific quality of life.

2. To examine the impact of improving symptoms of hayfever on examination performance of adolescents.

3. To assess the change in allergy practice, improvement in confidence and understanding, and management of allergy symptoms of trained healthcare professionals.

## Methods/Design

### Trial design

We are conducting a pragmatic cluster randomised trial. Trial practices will receive either i) allergic rhinitis and asthma management training with support materials (rhinitis management algorithm and leaflet) or ii) support materials alone.

### Eligibility of general practices for entering the trial

#### Inclusion criteria

• General practices within the recruitment areas of the Scottish Primary Care Research Network (SPCRN) and the Northern and Yorkshire Research Network (NYREN).

• Practices that agreed to participate in the study and were willing to allow healthcare professionals to attend a one-day short course on allergic rhinitis and asthma.

#### Exclusion criteria

• Practices not interested in participating and/or unable to release practice staff to attend the training.

### Eligibility of patients for entering the trial

All young people aged 12-18 years with hayfever were eligible to participate. Hayfever was defined by the presence of a documented clinician diagnosis in the patient's health record and any evidence of treatment used for allergic rhinitis. Patients were excluded if they were unable to give consent or were taking part in any other clinical trials involving treatments for allergic rhinitis.

### Recruitment

#### General practices and health care professionals

We applied to SPCRN and NYREN for their assistance with practice recruitment. They wrote to general practices informing them of the study with an information flyer. Additional contact was made with general practices in Scotland via NHS Education for Scotland (NES) and local informal contacts. Where practices expressed an interest in participating, an information sheet was sent to each practice with the offer of a face-to-face or telephone discussion at which the study was explained in more details. A member of the practice team (Lead GP or Practice Manager) then signed a consent form if the practice decided to participate. Practices were asked to nominate a member of their team who regularly sees patients with hayfever, but who has not previously received postgraduate allergy training. Twenty four general practices were recruited.

#### Patient recruitment

In order to avoid the risk of allocation bias, practices were asked to identify all eligible patients aged 12-18 years, through searches of the practice electronic medical record, prior to randomisation. Patients with a recorded diagnosis of hayfever (Read code clinical terms v2: H17), and/or evidence of use of hayfever medication (oral antihistamines and topical steroids, drugs used in nasal allergy and topical nasal decongestants; Read code clinical terms v2: c8, c6, 18 and 19) were eligible to participate. The practices were asked to write to eligible participants sending an invitation letter with a participant information sheet, consent form and patient data collection form for return directly to the study team. Two versions of the consent form were used, one for 12-15 year old participants, which included a space for parental/guardian consent, and one for 16-18 year old participants. All recruitment materials were approved by Lothian 2 Research Ethics Committee. Reminder invitations were sent to non-responders by the practice nurse two weeks after the initial mailing. Consenting patients were asked to express their preferred method of communication with the research team: email, text messages or post.

### Intervention

The intervention was in two phases: the first phase was at the level of the practice/HCP and the second at the level of the patient.

#### HCP training

Those practices randomly allocated to the intervention arm were invited to nominate a HCP to attend an allergic rhinitis and asthma short course run by Education for Health. The short course was delivered by Education for Health trainers; the programme for this course is available in Additional file 1. Those practices randomised to the control arm received written information.

#### Appointment with HCP (patients in both groups)

Once a patient had consented to take part in the trial by returning the signed consent and data collection forms, they were invited by email, text message or phone to make an appointment with the nominated HCP by the research team. The research team liaised with the general practice to ensure all consenting patients had made an appointment during May-June 2009/10. Patients were seen by the HCP in their usual clinic setting. No guidance was given to either group about the format of the consultation.

### Allocation of trial interventions

The general practice was the unit of allocation. Randomisation to intervention or control was carried out separately within each of the five participating regions: Lothian; Borders; Durham and Tees Valley; Northumberland Tyne and Wear, York. For the four regions with more than two practices, this was done using minimisation based on achieving optimum balance for practice list size (three strata <5000, >5001, but <10000, >10000 patients currently registered) and deprivation score (Index of Multiple Deprivation), according to the methods described by Carter and Hood [18]

The reason for randomisation by centre was to help ensure an even distribution of intervention and control practices as there is likely to be a geographical variation in pollen counts between centres.

### Outcome measures

#### Primary outcome

• The change in the RQLQ(S) score between baseline and 6 weeks post-intervention in the intervention and control groups.

The RQLQ(S) measures the problems experienced by young people with hayfever. This is a validated and widely used tool in clinical trials [12,17,19,20]. It has been designed to ask patients about seven domains: activity; sleep; non-nose/eye symptoms; practical problems; nasal symptoms; eye symptoms; and emotional function.

Quality of life using the validated RQLQ(S) was measured at the beginning of the hayfever season (March 2009) prior to the HCP clinic appointment, and repeated at six weeks post-intervention.

### Secondary outcomes

• Weekly pollen count data collected over the duration of trial.

#### Clinical outcomes

• Patient reported symptom scores using a visual analogue scale.

• Overall assessment of hayfever symptoms compared with the previous season.

• Number of general practitioner and practice nurse consultations for hayfever, prescribed (from clinical records) and over-the-counter (from patients) medication data were collected.

#### Educational outcomes

Educational data will be collected via the Local Education Authority. This will be based on final grades for the age-specific assessment adjusted for pre-trial grades, where possible.

#### Process outcomes: assessment of change in clinical practice

These were measured using a questionnaire assessing change in allergy practice and improvement in confidence, understanding and management of allergic symptoms. All HCPs in the intervention arm were asked to complete this questionnaire immediately before and after the training, and after seeing their last patient in the trial.

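### Professionals' knowledge and confidence are measured only in the trained arm, so the plan can describe their change but cannot attribute it to the course; the abstract also leaves out the control arm's materials

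*Protocol article*

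**What the plan says.** The Aims section sets out to "examine whether attending an allergic rhinitis and asthma short course can enhance knowledge and skills of practitioners" who see patients with hayfever, and lists changes in clinical practice alongside. Specific objective 3 is narrower: it concerns change in professionals who have been trained.

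The instrument, under Process outcomes, is a "questionnaire assessing change in allergy practice and improvement in confidence, understanding and management of allergic symptoms". Its administration is fixed there: "All HCPs in the intervention arm were asked to complete this questionnaire immediately before and after the training", and again once the professional has seen the last trial patient. No control-arm completion is mentioned anywhere in the article.

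The comparator is described in three ways:
- Trial design: "allergic rhinitis and asthma management training with support materials (rhinitis management algorithm and leaflet) or ii) support materials alone".
- HCP training: "Those practices randomised to the control arm received written information".
- Abstract: "Patients in the control arm will have a clinic appointment with their healthcare professional and will receive usual care".

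In both arms the research team invited consenting patients to book with the nominated professional, and neither arm was told how to run the consultation (Appointment with HCP). Control practices were offered the course only once the study had ended (Compliance).

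**The concern.** The Aims section asks a cause-and-effect question about the course. The trial randomises practices, so it has the comparator needed to answer it: control professionals who have the materials and see trial patients, but have not taken the course. The questionnaire is not given to them. An analysis plan cannot repair this, because it cannot recover data that were never collected.

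Two misreadings are at stake. A before-after gain could be reported as the effect of the course when part of it would have occurred without the course. And a reader of the abstract alone could take the trial as testing training against ordinary care, when the randomised contrast is training added to written materials and an invited appointment. A small effect means something different under each description.

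**Working it through.** The protocol gives no figure for this outcome, and its sample size concerns RQLQ(S) only. The check is therefore mainly a comparison of sections.

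**1. What each questionnaire interval contains.** By the Study timeline, training is in April and patient appointments are in May and June.

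| Interval (trained professionals) | What can contribute to the change |
|---|---|
| Just before to just after the course | The course; repeat testing; self-report straight after teaching; the materials, if handed out with the course (not stated) |
| Before the course to after the last patient | All of these, plus use of the materials, experience of the trial appointments, and the season |

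The course lasts one day, so season and appointments cannot explain the first interval. They can explain the second, which is the interval that speaks to changed practice.

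**2. What a control would remove.** Write observed change = course effect + background change. If background is a fraction f of the observed change, the course effect is (1 − f) × observed, and reading the whole change as the course effect overstates it by a factor of 1/(1 − f). The documents give no value for f, so these are assumptions:
- f = 0: factor 1.00
- f = 0.25: 1/0.75 = 1.33
- f = 0.50: 1/0.50 = 2.00

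Without control data, f cannot be estimated.

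**3. What can still be collected.** The article reports 24 practices in 2009, 12 per arm, and 10 further practices planned for 2010. Nine of the 12 control practices from 2009 have since attended the course, so an untrained measurement there is largely lost. Assuming an even split and one nominated professional per practice, 2010 offers 10/2 = 5 per arm.

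**4. Precision of 5 versus 5** (80% power, two-sided 5%):
- Normal approximation: (1.960 + 0.842) × √(2/5) = 2.802 × 0.632 = 1.77 SD.
- With the t distribution on 8 degrees of freedom: 2.02 SD.
- Adjusted for the first score, multiply by √(1 − r²). With an assumed correlation r = 0.3: 2.02 × 0.954 = 1.93 SD. With r = 0.7: 2.02 × 0.714 = 1.44 SD.
- 95% confidence interval half-width, unadjusted: 2.306 × 0.632 = 1.46 SD.

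For comparison, 12 versus 12 in 2009 would have given 2.802 × √(2/12) = 1.14 SD by the normal approximation.

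**5. The comparator label.** Trial design and HCP training agree that controls received written material. The abstract discloses the control appointment but not the materials.

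**The case against.** The strongest reply is that the measurement matches what objective 3 asks for. That objective concerns change in trained professionals, and nothing in the article promises a between-arm comparison on this questionnaire. This stands as far as it goes: the plan can describe that change. It does not remove the mismatch with the Aims section, which asks about the effect of attending.

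Second, the same-day measurement is largely free of season and appointment effects, and controls have no course day to serve as its counterpart. This also stands. It still leaves repeat testing and self-report straight after teaching uncontrolled, and it cannot show whether any gain lasted or changed practice.

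Third, consultation counts and medication data (Clinical outcomes) are not restricted to one arm, so changes in practice can be examined partly under randomisation. That is correct, but those data say nothing about knowledge or confidence.

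Fourth, usual care can be defended at patient level: patients were seen in the ordinary clinic, with no guidance to either arm on the consultation. The abstract is therefore incomplete rather than flatly wrong.

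Finally, about five per arm will not settle the causal question. This is accepted, and it is why rewording the aim is an adequate alternative.

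A reader might infer that the trial's claims about training are unsupported as a whole. The documents do not bear that out. RQLQ(S) is measured in both randomised arms, and both have the materials, so that contrast does estimate the added effect of training. The label in the abstract affects how the comparator is described, not whether the comparison is valid.

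**Conclusion.** The point holds for one secondary process outcome. As planned, the questionnaire gives an uncontrolled before-after change in trained professionals. That is enough to describe change, but not to conclude that attending the course caused it. The change to the last patient is the weakest evidence. The size of any bias is unknown: the factors of 1.33 and 2.00 above only illustrate assumed inputs. The primary analysis and the sample size are unaffected.

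A 2010 comparison of about 5 versus 5 would be informative only for differences near 2 SD, or roughly 1.4 to 1.9 SD after adjustment under the assumed correlations.

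The conclusion assumes that the article is complete in saying who received the questionnaire. The precision figures also assume an even split of the further practices and one professional per practice.

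The abstract's description of the control is a separate, smaller matter of reconciling it with the methods.

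**What to change.** - **2010 practices:** give control professionals the same questionnaire before the season and after their last trial patient, and before any course is offered to them. Report the between-arm difference adjusted for the first score, labelled exploratory and imprecise. The cost is one short questionnaire sent twice to about five people.
- **2009 data:** label them as an uncontrolled before-after change.
- **If 2010 control measurement is not possible** (for example, because the pre-season point has passed): reword the secondary aim as a descriptive before-after change in trained professionals, in line with objective 3. This costs wording only.
- **Abstract:** reconcile it with Trial design and HCP training by naming the support materials given to controls, and state the effect as that of training added to those materials and an invited appointment. This also costs wording only.
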